## Abstract

**Background:**

Cognitive impairment is a common dysfunction after stroke that seriously affects the overall recovery of patients. Cognitive rehabilitation training is currently the main treatment to improve cognitive function, but its curative effect is limited. Acupuncture is a core component of traditional Chinese medicine (TCM), and some previous clinical studies have shown that it might be effective in treating post-stroke cognitive impairment (PSCI), but further evidence from large-sample studies is needed. The overall objective of this trial is to obtain further data to develop an optimized acupuncture treatment for PSCI by comparing the effects of different acupuncture treatment methods on cognitive function in PSCI patients.

**Methods/design:**

In this multicenter, prospective, randomized controlled trial, 206 eligible stroke inpatients who meet the trial criteria will be randomly assigned to 2 groups: an electroacupuncture (EA) plus needle retention (NR) group and an EA group. Both groups of patients will undergo the same routine cognitive rehabilitation treatments. All treatments will be given 5 times per week for 8 weeks. The primary outcomes will be assessed using the Mini-Mental State Examination (MMSE) and the Montreal Cognitive Assessment scale (MOCA). The secondary outcome will be measured by the Barthel Index (BI). All outcomes will be evaluated at baseline, week 4, week 8, and the third and sixth month after the end of treatment.

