### Sample size

We will conduct this study using a randomized controlled trial design, and the main observed outcome will be improvements in patient cognitive function. Our previous small-sample (20 cases) clinical observation found that 2 weeks of EA plus routine cognitive rehabilitation treatment and EA plus NR and routine cognitive rehabilitation treatment can reduce scores on the MOCA scale by 3.17 ± 2.12 and 4.40 ± 2.59 points, respectively. With the significance test level set at 0.05 and the test power at 0.9, the sample size was calculated by using the following:
$$ N=2\times {\left[\left({z}_{\alpha /2}+{z}_{\beta}\right)\times \upsigma /\updelta \right]}^2 $$

*N* is the required sample size for each group, and the sample size of each group is equal. When *α* is 0.05 and *β* is 0.1, the normal distribution quantile table shows the following:
$$ {Z}_{\alpha /2}=1.96 $$

and
$$ {Z}_{\beta }=1.282. $$

*σ* and *δ* represent the larger standard deviation and the mean difference between two groups, which are 2.59 and 1.23, respectively. By substituting the above data into the formula, it was calculated that 93 patients will be needed in each group. Accounting for a 10% dropout rate, the final estimated sample size is approximately 103 patients in each group (206 in total).

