### Outcome measures

All participants will be evaluated at these time points: baseline, week 4, week 8, and follow-up week 12 and week 24 after all treatments are completed. All treatment evaluations will be conducted by researchers who will be blinded to the treatment allocation.

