### Statistical analysis

Statistical analysis of all data will be performed using SPSS 22.0 software by specialized statisticians who are not the principal researchers. Classified variables will be analyzed using Pearson’s *χ*^2^ test or Fisher’s exact test, and continuous variables will be evaluated using Student’s *t* test or an appropriate nonparametric method. The measurement data from different treatment groups will be statistically described by the mean ± standard deviation. When comparing within groups or between groups, a normality test and homogeneity of variance test will be performed before data analysis of each group. If the data satisfy the normal distribution and homogeneity of variance, then the *t* test will be used for comparison between two groups, and the LSD or SNK method will be used for multiple comparisons. Conversely, the rank-sum test will be used for nonnormality or nonuniformity of variance. The significance level used for statistical analysis with 2-tailed testing will be set at 5%.

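### Two primary scales, no primary visit or success rule, and a sample size for one MOCA test: the stated 5% error and 90% power hold together under neither natural success rule

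*Protocol article*

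**What the plan says.** The statements that have to fit together are all in the protocol article.

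- **Primary outcomes.** The abstract states: "The primary outcomes will be assessed using the Mini-Mental State Examination (MMSE) and the Montreal Cognitive Assessment scale (MOCA". The section Primary outcomes lists the same two scales, with no order between them and no rule for combining them.
- **Visits.** The abstract says: "All outcomes will be evaluated at baseline, week 4, week 8, and the third and sixth month after the end of treatment". Outcome measures gives the same schedule as "baseline, week 4, week 8, and follow-up week 12 and week 24 after all treatments are completed". That makes four post-baseline visits, and none is called primary.
- **Main outcome for planning.** In Sample size, "the main observed outcome will be improvements in patient cognitive function". This fixes neither a scale nor a visit.
- **Error and power for planning.** The same section sets them out: "With the significance test level set at 0.05 and the test power at 0.9".
- **Planning data.** They come from MOCA only, in a pilot of 20 patients treated for 2 weeks. The two regimens "can reduce scores on the MOCA scale by 3.17 ± 2.12 and 4.40 ± 2.59 points, respectively". No MMSE figure is given.
- **Analysis.** Statistical analysis plans t tests or rank-sum tests between the two groups, and says: "The significance level used for statistical analysis with 2-tailed testing will be set at 5" per cent. It also mentions LSD or SNK for multiple comparisons.

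**The concern.** An error rate and a power figure describe a trial only when it is clear which result counts as success. Here the 5% and the 90% were calculated for one comparison of one scale. The outcome section then declares two primary scales and leaves open which visit decides and whether one or both scales must show a difference.

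Two rules suggest themselves, and they fail in opposite ways. If a difference on either scale is enough, there are two chances of a false positive and the 5% is exceeded. If both scales must differ, the 5% is safe but the chance of success is lower than the 90% quoted. These are alternatives and do not add up.

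What is at stake is the meaning of the trial's main claim. As written, the deciding scale and visit could be settled after the results are known. Participants and acupuncturists are not blinded (section Blinding), which gives a further reason to fix the criterion in advance.

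**Working it through.** **Inputs from the protocol article (Sample size):** two-sided alpha 0.05, power 0.90, z values 1.96 and 1.282, SD 2.59, difference 4.40 - 3.17 = 1.23, dropout 10%.

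**Inputs assumed, because the document gives none:** the correlation between the MMSE and MOCA test statistics and between visits (shown as ranges), and MMSE power equal to that of MOCA.

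**Step 1. The plan's own figure.**
N = 2 × [(1.96 + 1.282) × 2.59 / 1.23]² = 2 × (6.827)² = 93.2 per group, stated as 93. With dropout, 93 / 0.9 = 103.3, stated as about 103. Power at 93 per group is 0.899. The figure reproduces, for one MOCA test.

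**Step 2. Either scale suffices, one visit.**
If the tests are independent, the chance of at least one false positive is 1 - 0.95² = 0.0975. For correlated tests, simulation from a bivariate normal distribution (1,000,000 draws) gives the third column below.

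**Step 3. Both scales must succeed, one visit.**
Type I error stays at or below 5%, since both tests must reject. With 90% power on each scale, joint power under independence is 0.9 × 0.9 = 0.81. The last column gives the simulated values for correlated tests.

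| Assumed correlation | Power, either scale | Type I error, either scale | Joint power, both scales |
|---|---|---|---|
| 0 | 0.990 | 9.75% | 0.81 |
| 0.5 | 0.968 | 9.1% | 0.83 |
| 0.7 | 0.953 | 8.3% | 0.85 |
| 0.8 | 0.944 | 7.8% | 0.86 |
| 0.9 | 0.931 | 7.0% | 0.87 |

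The either-scale rule therefore has the power but not the error rate. The both-scales rule has the error rate but not the power.

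**Step 4. Upper case: a win on either scale at any visit.**
The document does not state this rule. There would be 2 × 4 = 8 tests. If independent, the error is 1 - 0.95⁸ = 0.337. By simulation (400,000 draws) it is 26.9% with between-scale and between-visit correlations both 0.5, 17.2% with both 0.8, and 12.9% with both 0.9.

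**Step 5. What it would cost to keep both scales primary at 90% power,** taking the same difference and SD for MMSE:
- either scale, alpha split to 0.025 each: 111 per group, 111 / 0.9 = 123.3, so 124 with dropout; at 93 per group the power of each test would be 0.841;
- both scales required at 0.05 each: 106 to 115 per group for correlations 0.8 to 0, or 118 to 128 with dropout.

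With one scale at one visit as the single primary, the planned 93 (103 with dropout) stands, if the pilot difference and SD apply there.

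**The case against.** The strongest reply is that a protocol article may leave the primary visit, the success rule and the handling of multiplicity to the full protocol or an analysis plan, neither of which is shown. Taken alone, those silences would not be a finding. What remains is a mismatch between things the article does state: two primary scales, one 5% level, and a 90% power calculated on one of the two. A later hierarchy would have to override the equal primary status given here.

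Some stronger readings are tempting and should not be drawn.

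- *Eight tests are planned, each at 5%, so the false-positive rate is several times 5%.* The article says outcomes are evaluated at each visit. It does not say each visit is tested separately or that any visit can carry the claim. Trial design and Table 1 distinguish mid-treatment, end of treatment and follow-up, so the visits are not presented as interchangeable. The 13-27% range, and 33.7% under independence, belong only to that unstated rule.
- *MMSE has lower power than MOCA, so joint power is lower still.* The article gives no MMSE effect or SD, so no specific lower figure can be supported.
- *Calling MOCA more sensitive contradicts making MMSE primary.* The remark is limited to mild impairment, the trial is not restricted to mild cases, and both scales are used for eligibility.
- *Multiplicity is not mentioned at all.* LSD and SNK are named. They compare several group means, however, and with two arms they adjust nothing across scales or visits.
- *The sample size is miscalculated.* It is not.

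It is also fair that the Background calls the trial a preliminary experiment, which tempers the severity. The Discussion nevertheless looks to influence rehabilitation guidelines, and that use needs a fixed criterion.

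**Conclusion.** The point holds in a limited form and should be fixed. The stated 5% and 90% fit one MOCA comparison at one visit, which the protocol article never designates as the primary test. Under the two natural rules at a single visit, either type I error is 9.75% if independent (about 7-9% at correlations 0.9-0.5), or it is kept and joint power is about 0.81-0.87.

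The correlations are assumptions, and so is 90% power for MMSE. The direction does not depend on the exact correlation: over the whole range examined, one of the two stated figures is missed. The planning difference also comes from 2 weeks of treatment, so even for MOCA the 90% depends on that difference and SD holding at a visit the trial actually has.

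**What to change.** Name one primary endpoint: the between-group difference in MOCA change from baseline to week 8, the end of treatment. It uses the scale on which the sample size was built. Test MMSE at week 8 at two-sided 5% only if the MOCA test is significant. Treat week 4, both follow-ups and the Barthel Index as secondary or supportive. State that the 90% power refers to the MOCA test alone, provided the pilot difference of 1.23 and SD of 2.59 hold at week 8.

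If the sponsor prefers to keep both scales as required co-primaries, the deciding visit should still be named and the power restated as below 90% at the present sample size.

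The recommended change adds no patients and no visits. Its price is that MMSE loses equal primary status. Recruitment began on 1 December 2019, so this is a change of primary endpoint in an ongoing trial. It needs a protocol amendment with ethics committee approval, as the section Quality control requires for changes to the research plan, and a registry update. Both should be complete before the data are examined.

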**Discussion:**

Our aim is to evaluate the effects of two different acupuncture treatment methods for treating PSCI patients. This study is expected to provide data to be used in developing an optimized acupuncture treatment method for PSCI treatment.

**Trial registration:**

Chinese Clinical Trial Registry ChiCTR1900027849. Registered on 30 November 2019, http://www.chictr.org.cn/showproj.aspx?proj=46316

## Background

Stroke is the leading cause of death and disability worldwide and has a rising incidence and a high disability rate, often accompanied by many types of dysfunction [1–3]. Post-stroke cognitive impairment (PSCI) is a series of syndromes that meet the diagnostic criteria for cognitive impairment within 6 months after the occurrence of stroke and is observed after approximately 66% of strokes [4]. Furthermore, one study reported that the incidence of PSCI can be as high as 69.8% within 3 months of stroke [5]. PSCI mainly manifests as disruptions in advanced brain functions such as learning, memory, executive ability, and visual space/structural ability, which seriously affect patient quality of life (QOL) and overall rehabilitation [6, 7].

Management of vascular risk factors (hypertension, hyperlipidemia, diabetes, smoking, new atrial fibrillation and other arrhythmias) is critical, and the use of antiplatelet drugs (aspirin, clopidogrel, etc.) and anticoagulants is recommended according to the stroke prevention guidelines [8, 9]. In addition, the use of angiotensin-converting enzyme inhibitors and diuretics can delay the progression of white matter changes in patients with stroke [10]. Donepezil, galantamine, and memantine have been reported to improve cognitive function, but there are adverse reactions and certain risks [11–13]. A Cochrane review analyzed the efficacy of nondrug interventions focusing on cognitive rehabilitation for PSCI, and the results showed that more research evidence is needed [14]. Hyperbaric oxygen therapy and Tai Chi may contribute to cognitive improvements, but have not yet been proven to be effective independent therapies [15, 16]. Although there are multiple treatments, there are still few effective treatments for PSCI.

Acupuncture is a core component of TCM, and it has a definite effect on PSCI [17–19]. However, there are shortcomings such as numerous acupuncture points, inconsistent treatment times, and unclear cumulative effects of acupuncture and needle retention. At present, no unified acupuncture treatment method has been released. In addition, research on the dose-effect relationship of acupuncture is increasing year by year. However, whether needle retention can improve the efficacy of conventional EA therapy in patients with PSCI remains unclear. Therefore, to study the clinical efficacy and safety of EA and NR for PSCI, we designed this multicenter, prospective, large-sample randomized controlled trial with a sufficient follow-up period. As a preliminary experiment, we aim to observe the effects of EA treatment on cognitive function by subjective and objective assessments and to obtain further data to develop an optimized acupuncture treatment for PSCI. The results will be helpful to demonstrate whether EA plus NR treatment is an effective and safe therapy for improving cognitive function in patients with PSCI.

## Trial objectives

To observe and compare the difference between the two treatment methods in improving cognitive impairment and activities of daily living in patients with PSCI.To provide more evidence for developing an optimized acupuncture treatment method for PSCI treatment in the future.

## Methods/design

### Trial design

This is a multicenter, prospective, randomized controlled trial supported by the Henan Administration of Traditional Chinese Medicine. The trial will be jointly conducted by three centers in Zhengzhou, China: the First Affiliated Hospital of Henan University of Chinese Medicine, the Henan Province Hospital of TCM, and the Third Affiliated Hospital of Henan University of Chinese Medicine. A total of 206 patients who meet the predefined criteria will be randomly assigned to 2 groups, with one group receiving EA plus NR and routine rehabilitation treatment and the other group receiving EA plus routine rehabilitation treatment. After a 1-week washout period, patients will receive treatment 5 times a week over 8 weeks of observation. Participants will be assessed at 4 time points: baseline (0 weeks), the middle of the treatment (4 weeks after treatment starts), the end of the treatment (8 weeks after treatment starts), and follow-up (12 weeks and 24 weeks after treatment finishes). All participants will complete the MMSE, MOCA, and BI assessments. The study flow chart is shown in Fig. 1. The trial process chart is shown in Table 1.

**Fig. 1 Fig1:**
[figure not shown]
Flowchart of the trial

**Table 1 Tab1:** Timing of treatment assessments and data collection

	Study period					
	Enrolment	Baseline	Treatment phase		Follow-up phase	
Timepoint	− 1 week	0 week	4 weeks	8 weeks	12 weeks	24 weeks
Enrolment						
Eligibility screen	×					
Informed consent	×					
Medical history	×					
Merger disease	×					
Randomization		×				
Interventions						
Treatment group		×	×	×		
Control group		×	×	×		
Assessments						
MMSE		×	×	×	×	×
MOCA		×	×	×	×	×
BI		×	×	×	×	×
Safety evaluation		×		×		
Adverse events		×	×	×	×	×

### Ethics

This trial was approved by the ethics committee of the First Affiliated Hospital of Henan University of Chinese Medicine on 5 September, 2019 (reference number: 2019HL-102-01). All participants will sign an informed consent form, and to protect their privacy, their real names will not appear in related reports.

### Study setting

All participants in this trial will be recruited from the First Affiliated Hospital of Henan University of Chinese Medicine, the Henan Province Hospital of TCM, and the Third Affiliated Hospital of Henan University of Chinese Medicine. Interventions for all participants will be carried out in the hospitals where the participants are recruited. The First Affiliated Hospital of Henan University of Chinese Medicine will be responsible for this trial coordination and data management.

### Sample size

We will conduct this study using a randomized controlled trial design, and the main observed outcome will be improvements in patient cognitive function. Our previous small-sample (20 cases) clinical observation found that 2 weeks of EA plus routine cognitive rehabilitation treatment and EA plus NR and routine cognitive rehabilitation treatment can reduce scores on the MOCA scale by 3.17 ± 2.12 and 4.40 ± 2.59 points, respectively. With the significance test level set at 0.05 and the test power at 0.9, the sample size was calculated by using the following:
$$ N=2\times {\left[\left({z}_{\alpha /2}+{z}_{\beta}\right)\times \upsigma /\updelta \right]}^2 $$

*N* is the required sample size for each group, and the sample size of each group is equal. When *α* is 0.05 and *β* is 0.1, the normal distribution quantile table shows the following:
$$ {Z}_{\alpha /2}=1.96 $$

and
$$ {Z}_{\beta }=1.282. $$

*σ* and *δ* represent the larger standard deviation and the mean difference between two groups, which are 2.59 and 1.23, respectively. By substituting the above data into the formula, it was calculated that 93 patients will be needed in each group. Accounting for a 10% dropout rate, the final estimated sample size is approximately 103 patients in each group (206 in total).

### Inclusion criteria

Participants meeting the following criteria will be included:
Male or female participants aged 30–75Participants who meet the diagnostic criteria of stroke by computed tomography (CT) or magnetic resonance imaging (MRI)Participants with cognitive impairment identified with the MMSE scale and MOCA assessment scalePatients with cognitive impairment that occurred after stroke, and not for other reasonsPatients with a disease course between 1 month to 1 year who did not use any cognitive enhancing drugs before enrollmentPatients with clear consciousness and stable vital signsPatients who voluntarily agree with the investigation and sign a written informed consent form for the clinical trial

### Exclusion criteria

Participants who report any of the following conditions will be excluded:
Patients with non-stroke diseases that can cause cognitive impairment such as intracranial space occupying lesions, brain trauma, and aneurysmsPatients with diseases that seriously affect cognitive tests, such as abnormal audiovisual functions and mental disordersPatients with a significant history of cognitive decline or dementia prior to this stroke onsetPatients with other serious diseases such as immune diseases, endocrine diseases, and abnormal liver and kidney functionsPregnant or lactating womenPatients participating in other clinical trials that could affect the evaluation of this study’s results

### Elimination criteria

Patients who do not meet the criteria for a diagnosis of PSCI and are mistakenly includedPatients with poor compliance or self-withdrawal, or patients who are judged by the investigator as unsuitable to continue the trial because of serious adverse complications

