#### EA group

In addition to routine cognitive rehabilitation treatments, the intervention of this group will be the same as that in the EA plus NR group except that the needles will be directly removed after 30 min of electrical stimulation. There will be no NR process.

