### Safety evaluation and adverse events

The safety evaluation mainly refers to the evaluation of safety indicators and adverse events. The safety indicators will be tested once before and after the treatment and will include a general physical examination (blood pressure, breathing, pulse), routine blood tests, routine urine tests, routine stool tests, electrocardiograms, and liver and kidney function tests. Adverse events in this study will be defined as any discomfort, symptoms, or diseases that occurred during this acupuncture clinical trial, such as fainting, allergies, or pain. If someone faints, researchers will immediately remove needles, then keep the patient in a supine position in a ventilated place, and give him/her warm water or sugar water to let him/her fully rest until the body recovers. If allergies or pain occurs, needles will be immediately withdrawn, and the patient will be treated symptomatically. All the above detailed information regarding safety evaluations will be reported in detail in case report forms (CRFs), and the impact of all adverse events will be analyzed at the end of the study. Participants who experience adverse events will be compensated accordingly.

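### The elimination criteria take randomised patients out for compliance, withdrawal and complications that treatment can cause, which exposes the group comparison to bias of unknown size and direction

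*Protocol article*

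**What the plan says.** The Elimination criteria section has two items. The first covers patients without a PSCI diagnosis who were included by mistake. The second covers poor compliance, self-withdrawal and "patients who are judged by the investigator as unsuitable to continue the trial because of serious adverse complications". The section gives no compliance threshold and does not say what elimination entails: stopping treatment, stopping follow-up or removal from analysis.

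The arms differ in session length. Under EA plus NR, the needles stay in for 1 h after 30 min of stimulation, with manipulation every 30 min. In the EA group, "the needles will be directly removed after 30 min of electrical stimulation". Both arms are treated 5 times a week for 8 weeks. The Blinding section says a double-blind design was not possible and that outcome assessors are blinded; the Intervention section adds that the rehabilitation therapists are blinded.

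Safety is a stated purpose: the Background says the trial was designed "to study the clinical efficacy and safety of EA and NR for PSCI". The safety section defines adverse events as "any discomfort, symptoms, or diseases that occurred during this acupuncture clinical trial" and says that "the impact of all adverse events will be analyzed at the end of the study". On laboratory and ECG tests it says: "The safety indicators will be tested once before and after the treatment". Table 1 places the safety evaluation at baseline and week 8, and adverse events at baseline and weeks 4, 8, 12 and 24.

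**The concern.** Mistaken inclusion is a fact fixed before randomisation. If it is judged blind to arm, removing such patients need not disturb the balance that randomisation gives. Poor compliance, withdrawal and serious complications arise afterwards and can be consequences of the allocated treatment. Removing patients on those grounds leaves two groups selected by how well they tolerated different regimens.

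Two features make unequal selection plausible here. The regimens differ in the very burden that drives compliance and withdrawal. The grounds also leave room for judgement, because compliance has no threshold and suitability is for the investigator to decide in a trial that is not double-blind.

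At stake is the randomised comparison on MMSE, MOCA and BI. If these patients stop being assessed, no later analysis can recover outcomes that were never collected.

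**Working it through.** **1. The plan's own figure.** The Sample size section gives SD 2.59, difference 1.23, z values 1.96 and 1.282, and 10% dropout.

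- N = 2 × [(1.96 + 1.282) × 2.59 / 1.23]² = 93.2 per group (stated: 93).
- 93 / 0.9 = 103.3 (stated: about 103).

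The sample size reproduces. The allowance is 103 − 93 = 10 patients per arm. Power is 92.6% with 103 per arm and 89.9% with 93, so losing the planned 10% costs little power. The issue is bias, which a larger sample does not remove.

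**2. Burden by arm.** There are 5 × 8 = 40 sessions in each arm. An EA plus NR session lasts 30 + 60 = 90 min and an EA session lasts 30 min.

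**3. Illustration of bias in the MOCA difference.** From the document: pilot changes of 4.40 (EA plus NR) and 3.17 (EA), difference 1.23. These are two-week changes. The Sample size section words them as reductions; I treat them as gains. My assumptions: a fraction a is eliminated in the EA plus NR arm and b in the EA arm, the remaining patients show the pilot gains, and eliminated patients show none.

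- Difference with all randomised patients = (1 − a) × 4.40 − (1 − b) × 3.17.
- Difference after elimination = 1.23.
- Overstatement = a × 4.40 − b × 3.17.

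| a | b | Calculation | Overstatement | Share of 1.23 |
|---|---|---|---|---|
| 10% | 10% | 0.440 − 0.317 | 0.12 | 10% |
| 10% | 5% | 0.440 − 0.1585 | 0.28 | 23% |
| 15% | 5% | 0.660 − 0.1585 | 0.50 | 41% |
| 5% | 10% | 0.220 − 0.317 | −0.10 | −8% |

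The last row shows that the sign reverses if elimination is heavier in the EA arm.

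Zero gain is an extreme assumption. If eliminated patients lose only a share k of their arm's gain, each figure is multiplied by k. At k = 0.5 the first three rows become 0.06, 0.14 and 0.25.

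**4. Effect on the test when there is no true difference.** Suppose a fraction f is eliminated from the EA plus NR arm only, and those patients' change is worse by g points. The shift is f × g, with standard error 2.59 × √(1/[103(1 − f)] + 1/103). For f = 10% and g = 2.59, the shift is 0.26 and the two-sided type I error is about 0.107 instead of 0.05. Over f = 5% to 15% and g = 1.23 to 4.40, the shift runs from 0.06 to 0.66 points and the error from 0.053 to 0.42. Both f and g are assumptions.

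**5. Safety passages side by side.** The safety section promises analysis of all adverse events, and Table 1 schedules their collection to week 24. Neither exempts eliminated patients. The Elimination criteria section does not say whether those visits continue after elimination. The text places the safety tests after the treatment, while Table 1 places them at week 8. For a patient who stops in week 3, the document does not say which applies.

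**The case against.** The strongest reply is that elimination is never defined. Unsuitability to continue could mean discontinuation only, the Sample size section speaks of dropout, and the analysis section opens with "Statistical analysis of all data will be performed using SPSS 22.0 software". This stands in part: removal from the comparison is the natural reading, not a stated fact. The reading is natural because the clause speaks of continuing the trial, not the treatment, and because one heading gives these patients the same consequence as those included by mistake. A reference to all data does not help where data cease to be collected.

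Analysis sets are commonly left to the SAP or the full protocol, and neither is shown. That is right, and the point does not rest on their absence. It rests on a stated rule about who stays in the trial.

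The magnitudes depend on assumed elimination rates and outcomes. That stands. Eliminated patients may also have received cognitive rehabilitation, so zero gain is probably too severe.

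A reader might go further and infer that serious harms vanish from the safety record. The document does not support this: it promises analysis of all adverse events and schedules them at every visit. Nor does it support the inference that the bias must favour EA plus NR; heavier loss in the longer-session arm is plausible but not documented. It also does not say whether the investigator who judges suitability knows the allocation.

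**Conclusion.** The concern holds for the group comparison. The protocol lists post-randomisation grounds that treatment can cause as reasons for elimination, one of them without a threshold and one left to judgement, in a trial that is not double-blind and whose arms differ threefold in session length. This exposes the MMSE, MOCA and BI comparisons to selection bias.

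Size and direction cannot be determined from the document. Under the zero-gain assumption the MOCA difference would be overstated by 0.12 to 0.50 points in the three scenarios in which EA plus NR loses at least as many patients as EA. Smaller losses of gain give proportionately less, and the reverse imbalance can understate the difference.

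On safety, the finding is limited to two unclear points to reconcile: whether adverse events of eliminated patients are counted, and when the post-treatment tests apply to those who stop before week 8.

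**What to change.** Amend the Elimination criteria section as follows.

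- Keep mistaken inclusion as a separate ground, judged on pre-randomisation data by someone blind to arm.
- State that patients who comply poorly, withdraw from treatment or are judged unsuitable to continue keep their scheduled MMSE, MOCA, BI and adverse event assessments unless they withdraw consent, and are compared in the arm to which they were randomised.
- Leave the clinical decision to stop treatment, and the management of any event, with the investigator as now.
- Reconcile the section with the safety section and Table 1: state that adverse events of eliminated patients are counted, and clarify when the post-treatment safety tests apply to patients who stop before week 8.

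The cost is a wording amendment with ethics approval and continued contact with perhaps 10 patients per arm at visits already scheduled. The effect estimate will be somewhat diluted, because it will include patients who stopped early.
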